### Recruitment (15)

Potential participants will be recruited from among all respondents to the WHO-WMH-ICS mental health survey, currently administered to first-term students in multi-year educational programs at 15 universities and colleges in Sweden. Additional higher education institutions may be added. The invitation to survey respondents is sent out one term later, 4 to 6 months after completion of the survey, a time period sufficient for mental health status to change. This is the rationale for inviting *all* respondents rather than restricting invitations to individuals who already exhibit symptoms of mild to moderate depression and/or anxiety in the baseline epidemiological survey. Up to three reminders are sent after invitation.

## Assignment of interventions: allocation

Consenting participants are included in the study if their symptoms of depression and/or anxiety, as reported in the T0 treatment eligibility screening questionnaire (see Table 2), correspond to a mild to moderate level of severity. If they complete the pre-treatment assessment at T1 (see Fig. 1 and Table 2), they are allocated to one of the three study arms.

### Sequence generation (16a)

A randomization sequence is generated in blocks of 12 (3 × 4) and then matched to the list of participants who have qualified for randomization.

### Procedure for unblinding if needed (17b)

Since blinding does not hold for those directly involved in everyday implementation and participation in the trial, no unblinding procedure has been conceived.

## Data collection and management

### Plans for assessment and collection of outcomes (18a)

Data are collected at treatment eligibility screening, pre-treatment, mid-treatment, post-treatment, and 6, 12, and 24 months after randomization. In addition, weekly measures of depression, anxiety, and well-being are collected during treatment (see Table 2).

### Plans to promote participant retention and complete follow-up (18b)

There is a concern that participant attrition from follow-up will be higher than expected. Research interns, available from the spring of 2024, will be tasked with contacting participants at follow-up times, pending ethical approval.

### Confidentiality (27)

Data are stored in accordance with the DMP for the project and are managed according to the General Data Protection Regulation (GDPR) that covers personal data management in the European Union. Raw trial data are not currently shared with the WHO-WMH-ICS consortium.

## Analysis

### Statistical methods for primary and secondary outcomes (20a)

We will keep participants in the groups to which they were randomized in all analyses (intention-to-treat). We will conduct both available data analyses and analyses with missing data imputed using multiple imputations with chained equations (generating 200 datasets using 30 iterations of predictive mean matching). Both available data and imputed data analyses will be used to interpret findings.

All models of primary and secondary outcomes will be estimated using both Bayesian inference and maximum likelihood estimation [59]. The former will estimate the posterior distribution over effect estimates, while the latter will be used for null hypothesis testing. We will use (half) Student’s *t* priors for covariates, fixed intercepts, and error terms (centered at 0, with a scale of 2.5 and 3 degrees of freedom). Adaptive intercepts in multilevel models will be given standard normal priors. For point estimates, we will report the median of the posterior distribution of each parameter of interest (i.e., group contrasts), along with 95% compatibility intervals defined by the 2.5 and 97.5% percentiles of the posterior distributions. We will use the posterior probability of effect and *P*-values for our scientific inference.

The two co-primary outcomes, anxiety and depression, will be standardized and modeled using a multilevel linear regression model. The models will include a time-by-group interaction with time modeled as a dummy categorical variable (0 = T3, 1 = T4, 2 = T5, 3 = T6), as will group (0 = waiting list, 1 = unguided, 2 = guided). The models will be adjusted for baseline (T1) measures of the outcome variables (respectively) using a baseline-by-time interaction term and further adjusted for age, gender, and a binary variable indicating HBTQ (0 = No, 1 = Yes). Adaptive intercepts will be added to the models at the participant and university level. The linear combination of coefficient estimates for the group and time-by-group covariates will be used as effect estimates (i.e., differences between groups at the different follow-up intervals). For our primary contrasts (guided vs. waiting list and unguided vs. waiting list), we will report effects at T3 and T4. For our exploratory contrast (guided vs. unguided), we will report effects at all four follow-up intervals.

The secondary outcomes will be modeled similarly to the primary outcomes. The only exception is comorbidity, measured using DSM-5 CCSM, which results in the classification of participants concerning several conditions. We will use multilevel negative binomial regression to analyze the number of conditions participants are positive for (and fall back to Poisson regression if the outcome is not over-dispersed). In addition, DSM-5 CCSM is not measured at baseline (T1) but is measured at trial eligibility assessment (T0); thus models for DSM-5 CCSM will be adjusted for T0 measures.

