21. *TIC-P* Healthcare consumption and productivity loss in patients with a psychiatric disorder (56 items); Bouwmans et al., 2013 [56]

22. *CSQ* Client Satisfaction Questionnaire (8 items), Attkisson & Zwick 1982 [57]

22.1. *CSQ, adapted* Client Satisfaction Questionnaire (8 items), adapted for mid-Tx assessment

23. *NEQ* Negative treatment effects questionnaire (20 items), Rozental et al. 2019 [58]

24. *Qualitative interview* Qualitative interview on experience of treatment intervention

The algorithm will build on data from the PHQ-9 and GAD-7 questionnaires, where data for all three timepoints will be entered for each questionnaire separately, as follows: [(T0 + T1)/2] − T2. If the outcome of the algorithm is equal to £0 for either PHQ-9 or GAD-7, or both, the participant will be randomized to the ATS, or to continue in the treatment arm to which they were assigned at the start of the main trial. See under “Interim analyses (21b)” for a more detailed description. Randomization will be conducted via SPSS version 28.0 using an outcome of the exact number of randomized individuals, stratified by group allocation to guided or unguided treatment. Participants with missing data at any of these timepoints will not be included in the SWAT since unsuccessful attempts will have already been made to encourage them to respond, and dropout from the main trial seems likely.

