### Sample size (14)

We calculated the required sample size based on the smallest effect size on primary outcomes that we did not want to miss, with respect to the contrast between the guided intervention and waiting list control at 6 months post-randomization (T4). We estimated this effect size to 0.3 Cohen’s *d*. With a significance level of 0.05 (alpha) and power of 0.8 (beta), a two-sided *t*-test would require 176 individuals per group, giving a total of 528. Assuming an attrition rate of 40% at T4, this means that we should recruit at least 880 participants. Notwithstanding this power calculation, we hope to extend our recruitment sample to up to 1200 participants if possible, given additional possible attrition after T4 and the importance of reporting outcomes over a longer term than 6 months.

Regarding analysis of the SWAT comparing adapted versus continued standard treatment for at-risk participants, earlier work evaluating for insomnia [33] suggests that between-group differences in final scores corresponding to *d* = 0.4 are possible, which would require *n* = 100 + 100 at-risk participants, i.e., well within the recruitment target.

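### The co-primary models adjust for the T1 score only, although a second pre-randomization PHQ-9 and GAD-7 score (T0) is already held; adding it is a small, nearly free gain in precision

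*Protocol article*

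**What the plan says.** Section 20a lists the covariates of the co-primary models. The only symptom score is the T1 value of the outcome being modeled: "The models will be adjusted for baseline (T1) measures of the outcome variables", entered with a baseline-by-time interaction. Age, gender and a binary HBTQ indicator complete the list, with intercepts for participant and university. Most secondary outcomes are modeled in the same way.

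Table 2 schedules PHQ-9, GAD-7 and WHO-5 at both T0 and T1. The section on allocation says that inclusion is decided on the T0 symptom scores and that participants are allocated once they have completed T1.

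Two other places use T0:
- The SWAT entry rule takes the mean of T0 and T1 minus T2. It says that "data for all three timepoints will be entered for each questionnaire separately".
- The comorbidity outcome has no T1 measurement, "thus models for DSM-5 CCSM will be adjusted for T0 measures".

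The SWAT analyses reuse the primary models within the guided and unguided arms, with the SWAT contrast in place of the group contrast.

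**The concern.** T0 and T1 are two noisy readings of the same construct, and treatment can affect neither. A second reading usually explains some outcome variance that the first does not. Every eligible randomized participant should have the T0 PHQ-9 and GAD-7 scores, because eligibility was decided on them, so including them creates no missing covariate data. The covariate list is stated explicitly and T0 is not on it.

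What is at stake is precision in each primary contrast at T3 and T4, in a trial that expects to lose 40% of participants by T4. The comparison within the SWAT is smaller (100 + 100 planned), so precision matters more there.

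**Working it through.** **The plan's own figures.** Inputs from Sample size (14): "We estimated this effect size to 0.3 Cohen’s" *d*, two-sided alpha 0.05 and power 0.80. A two-sample *t*-test needs 175.4 per group, so 176. Then 3 × 176 = 528 and 528 / (1 − 0.40) = 880. This reproduces "would require 176 individuals per group, giving a total of 528" and the target of 880. The calculation is unadjusted, so it does not depend on which baseline scores enter the model.

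**Formulas.** Let r1 be the T1–outcome correlation, r0 the T0–outcome correlation and r01 the T0–T1 correlation.
- T1 only: R² = r1².
- T0 and T1: R² = (r0² + r1² − 2·r0·r1·r01) / (1 − r01²).
- Residual variance ratio = (1 − R² with both) / (1 − R² with T1 only). The SE ratio is its square root.
- The gain is exactly zero when r0 = r1·r01, that is, when T0 carries nothing beyond T1.

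**Assumptions.** The documents give no correlations. Assumed: r1 = 0.4 to 0.6, r01 = 0.6 to 0.8, and r0 equal to r1, up to 0.10 below it, or at the zero-gain value.

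**Central cases (r1 = 0.5, r01 = 0.7).** With T1 only, R² = 0.25.
- r0 = 0.50: R² = (0.25 + 0.25 − 0.35) / 0.51 = 0.294. Variance ratio 0.706 / 0.75 = 0.941; SE down 3.0%.
- r0 = 0.45: R² = (0.2025 + 0.25 − 0.315) / 0.51 = 0.270. Variance ratio 0.730 / 0.75 = 0.974; SE down 1.3%.

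**In power and sample size** (normal approximation, *d* = 0.3, 176 complete per group, SD = √(1 − R²)):

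| Adjustment | Power | n per group for 80% power |
|---|---|---|
| None | about 80% | 175 (176 by *t*-test) |
| T1 only | 90.1% | 131 |
| T1 and T0, r0 = 0.45 | 90.9% | 128 |
| T1 and T0, r0 = 0.50 | 91.8% | 124 |

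**Whole grid.** Variance falls by 0% to 14%, SE by 0% to 7.3%, and power rises by 0 to 2.7 points. The upper end needs r0 = r1 = r01 = 0.6: R² goes from 0.36 to 0.288 / 0.64 = 0.45, and the variance ratio is 0.55 / 0.64 = 0.859.

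**Range restriction.** Eligibility truncates T0 (PHQ-9 from 5 to 19 and/or GAD-7 of 5 or more). A simulation kept only rounded T0 scores of 5 to 19, with an assumed mean of 8 or 10 and SD of 5.5. For r0 = r1 = 0.5 and r01 = 0.7 the variance ratio moved from 0.941 to about 0.963. For r0 = 0.45 it moved from 0.974 to about 0.984. Over all simulated cases variance fell by 1.6% to 8.7% and SE by 0.8% to 4.4%. Because of the and/or rule, some participants qualify on the other scale, so truncating one score to 5–19 may overstate the restriction.

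**SWAT.** T2 is collected in week 3 and read before the second randomization, and anyone missing T0, T1 or T2 is left out of the SWAT. T2 is therefore a complete, pre-randomization score there and the most recent one. Its gain is not quantified, because the documents give nothing to base it on.

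**The case against.** The strongest case against is that nothing here is wrong. Adjusting a randomized comparison for the latest pre-randomization score, with a baseline-by-time term, is standard, valid and prespecified. T1 already delivers most of the benefit (about 80% to 90.1% power at r1 = 0.5), the extra gain rests on assumed correlations and may be zero, and recruitment may go up to 1200. The 14% extreme is also implausible: T0 would have to predict the outcome as well as the later T1 score does, and correlate with T1 no better than with outcomes months later. All of this stands and limits the point to an optional improvement.

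A reader might also infer more than the documents support:
- *That the plan itself relies on averaging T0 and T1 for precision.* The SWAT sections give no reason for averaging. A rule that classifies individuals also sets no standard for a covariate in a group comparison.
- *That the comorbidity model shows an inconsistency.* It uses T0 because that instrument has no T1 measurement. T1 where it exists and T0 otherwise is a consistent rule.
- *That eligibility guarantees T0 for WHO-5 too.* WHO-5 is scheduled at T0 but is not an eligibility criterion.
- *That T0 would offset the 40% attrition.* A covariate does not recover missing outcomes. It could inform the imputation, but the article does not list the imputation predictors, which is commonly left to the full plan.

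**Conclusion.** The point holds as a modest missed efficiency in the PHQ-9 and GAD-7 models. T0 precedes randomization, should be available for every eligible randomized participant, and is absent from a stated covariate list. The likely gain is about 1% to 3% in SE (3% to 6% in residual variance) in the central cases, within an assumed range of 0% to 14% in variance; range restriction tends to lower it. These figures treat one follow-up time and ignore the other covariates and the university intercept.

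It would be wrong to read this as bias, as an invalid primary analysis or as a fault in the 176, 528 or 880 figures. Those reproduce and are unaffected.

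**What to change.** Before outcomes are seen by arm:
- In the PHQ-9 and GAD-7 models, add the T0 score of the same outcome and a T0-by-time term alongside the T1 terms. Do the same for WHO-5 where T0 is available.
- Include T0 in the imputation model, so that it matches the analysis model.
- In the SWAT models, add the T2 score with its time term first; T0 is optional. T2 must stay out of the three-arm models, where it is measured after randomization.

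With four follow-up times, each added score costs four coefficients per model (one main effect and three interactions). No new data are needed and the sample size stays as it is. If the team prefers T1 alone, one sentence giving the reason would close the point.

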### Outcomes (12)

#### Primary outcome

The trial has two co-primary outcomes, assessed in all participants regardless of treatment received. The primary contrasts are guided vs. waiting list and unguided vs. waiting list.Anxiety, which will be measured using GAD-7 (total score).Depression, which will be measured using PHQ-9 (total score).

Although participants choose a primary treatment focus on anxiety or depression, most are expected to exhibit baseline symptoms for both disorders. For this reason, the two co-primary outcomes are assessed and analyzed among all participants.

Primary outcomes are assessed 10 weeks post-randomization (T3 post-treatment measure), 6 months post-randomization (T4), 12 months post-randomization (T5), and 24 months post-randomization (T6). After T4, participants in the waiting list control group will be offered the unguided version of the interventions; thus, we will use T3 and T4 measures for contrasts among all three groups and all follow-up interval measures for contrasts between guided and unguided groups (adjusted for baseline measures).

See Fig. 1a for a complete SPIRIT checklist, Fig. 1b for the participant timeline, Fig. 2 for a TIDieR checklist regarding the intervention description, Fig. 3 for a CONSORT flow diagram, Table 1 for an overview of the intervention modules, and Table 2 for a complete, referenced list of the assessment instrument used in the study.

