#### Ancillary analyses

We will conduct effect modification analyses by introducing interaction covariates into the regression models with respect to age, gender, HBTQ, and each respective outcome at baseline. The posterior probability of interaction effects and the Watanabe-Akaike information criterion (WAIC) will be used for scientific inference from the effect modification models.

Systematic attrition to follow-up at the different time intervals will be studied by estimating the odds ratio of not responding conditional on age, gender, HBQT, and the two co-primary outcome variables measured at baseline.

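### Each co-primary model adjusts for its own T1 score but not for the other scale's; adding the second T1 score is a nearly free improvement, not the repair of an error.

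*Protocol article*

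**What the plan says.** Under Statistical methods for primary and secondary outcomes (20a), each co-primary model is "adjusted for baseline (T1) measures of the outcome variables (respectively"), and the effect of that baseline score may vary by follow-up time. The other covariates are age, gender and an HBTQ indicator, with intercepts for participant and university. The word in brackets settles the matter: of the two scales, each model contains only its own.

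Four other places bear on this choice:

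- Ancillary analyses, under Methods for additional analyses (20b), studies non-response "conditional on age, gender, HBQT, and the two co-primary outcome variables measured at baseline". Age, gender and HBTQ are already in every outcome model. The other scale's T1 score is the one variable on that list that a given co-primary model leaves out.
- Primary outcome, under Outcomes (12), says of participants that "most are expected to exhibit baseline symptoms for both disorders".
- Assignment of interventions: allocation makes T1 a condition of randomization: "If they complete the pre-treatment assessment at T1 (see Fig. 1 and Table 2), they are allocated to one of the three study arms". Table 2 has both PHQ-9 and GAD-7 at T1.
- Missing data are met with an available-data analysis and multiple imputation, and "Both available data and imputed data analyses will be used to interpret findings". Sample size (14) plans on substantial loss: "Assuming an attrition rate of 40% at T4".

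**The concern.** A likelihood-based analysis of available data is protected against dropout to the extent that dropout is explained by what the model contains. A baseline score that predicts both the outcome and dropout, and sits outside the model, can leak into the arm contrast when its relation to dropout, or the amount of dropout, differs between arms. Here that score exists for everyone randomized and costs nothing to include.

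Precision is also at stake. A second prognostic baseline lowers residual variance whatever the dropout pattern. The specification is shared by all eight primary comparisons (two outcomes, two contrasts, T3 and T4) and is passed on to the SWAT and mediation models.

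**Working it through.** **The plan's own figure.** A two-sided t-test with d = 0.3, alpha 0.05 and power 0.8 needs 175.4, so 176 per group. Then 3 × 176 = 528, and 528 / (1 − 0.40) = 880. The stated numbers reproduce, and nothing below changes them.

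**Assumptions not in the documents.** Correlation of own T1 score with follow-up, r_own = 0.4-0.5; of the other T1 score with follow-up, r_cross = 0.35-0.45; between the two T1 scores, b = 0.5-0.6. From the plan: d = 0.3 and dropout p = 0.40 at T4.

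**Precision.** The proportional fall in residual variance is (r_cross − r_own·b)² / [(1 − r_own²)(1 − b²)].

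| r_own / r_cross / b | Calculation | Fall |
|---|---|---|
| 0.5 / 0.35 / 0.6 | 0.05² / (0.75 × 0.64) | 0.5% |
| 0.5 / 0.40 / 0.6 | 0.10² / (0.75 × 0.64) | 2.1% |
| 0.5 / 0.45 / 0.5 | 0.20² / (0.75 × 0.75) | 7.1% |
| 0.4 / 0.45 / 0.5 | 0.25² / (0.84 × 0.75) | 9.9% |

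A fall of 2.1% is worth about 0.021 × 528 = 11 analysed participants. The last row assumes that the other scale predicts the outcome better than its own baseline does, so it is an outer limit.

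**Bias in the available-data contrast.** Let the log-odds of dropout per SD of the other T1 score be g0 and g1 in the two arms. To first order, completers' mean on that score shifts by −p·g. The own T1 score absorbs a share b² of this, and the remainder (1 − b²) acts through the partial coefficient (r_cross − r_own·b)/(1 − b²). So the absolute bias is about p × |g1 − g0| × (r_cross − r_own·b), where the last factor runs from 0.05 to 0.25.

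- Odds ratio 1.5 per SD in both arms, 40% dropout in each: g1 − g0 = 0, so no bias.
- Odds ratio 1.0 against 1.5: 0.40 × 0.405 = 0.162, giving 0.008 to 0.041 SD. The top value comes from the outer-limit row; 0.5/0.45/0.5 gives 0.032. Simulation over a partial coefficient of 0.1-0.3 and b of 0.5-0.7 gave 0.007 to 0.034.
- Same odds ratio of 1.5 but 30% against 50% dropout: 0.405 × 0.20 = 0.081, giving 0.004 to 0.020 SD. With an odds ratio of 2 and a partial coefficient of 0.3, simulation gave 0.025.
- Opposed log-odds, ±0.2: 0.40 × 0.4 = 0.16, giving 0.008 to 0.040 SD. With ±0.4: 0.40 × 0.8 = 0.32, giving 0.016 to 0.080 SD.

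In the simulations, adding the second T1 score brought the bias to about 0, within simulation error of roughly 0.001-0.004 SD.

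**Does T3 rescue T4?** I fitted a two-timepoint random-intercept model with monotone dropout (assumed 30% at T3, 40% at T4, residual within-person correlation 0.5). With own T1 only, the T4 bias was 0.015 (0.5/0.40/0.6) and 0.029 SD (0.5/0.45/0.5) for odds ratios 1.0 against 1.5, and 0.025 and 0.054 SD for ±0.4. The formula gives 0.016, 0.032, 0.032 and 0.064. Observed T3 scores absorb part of the bias, not most of it. With both T1 scores it stayed within 0.004 SD of 0.

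**Consequence.** With 176 per arm, the standard error is √(2/176) = 0.107 SD. A bias of 0.02 SD toward the null takes power from 80% to about 75%, and 0.03 SD to about 72%. The direction is not known; a bias away from the null would instead flatter the treatment.

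**The case against.** The strongest reply is that nothing here is wrong. Own-baseline adjustment with a by-time interaction, three further covariates and random intercepts is a standard prespecified model. That stands, and it is why this is an improvement and not a defect.

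A reader might infer more from the plan than it supports:

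- That the plan expects dropout to be driven by the two scales. It does not say so. The attrition analysis is a routine description of who is lost, and it states no arm term or arm interaction.
- That the available-data contrasts are therefore biased. A predictor of dropout does not by itself bias an arm contrast; its effect, or total dropout, must differ by arm. The arms do differ in human contact, and the Background cites early studies in which guidance reduced attrition, so a difference is plausible. It is not established for this trial.
- That one covariate removes attrition bias. It removes only the part explained by the other T1 score. Dropout driven by symptoms after T1 is untouched. So is effect modification by the other scale: a simulated case left 0.013 SD with and without the covariate.
- That the bias figures cover all eight comparisons. The 40% loss is stated for T4; no figure is given for T3.

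The imputation analysis may already use both T1 scores. Its variable list is not given and may properly sit in a statistical analysis plan, so its absence is no finding. But it would not change the available-data result, which the plan also uses to interpret findings.

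**Conclusion.** A worthwhile, low-priority refinement. The certain part is that each co-primary model leaves out a collected, probably prognostic baseline score. The sure benefit is modest: a 0.5-10% fall in residual variance under the assumed correlations.

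The protection against bias is conditional. It is nil with equal dependence and equal dropout across arms, and roughly 0.01-0.03 SD (3-10% of the 0.3 target) under moderate differences. It reaches about 0.08 SD only when dropout is strongly opposed between arms and the most favourable correlations hold. The moderate values are well inside one standard error. All correlations and dropout odds ratios are assumptions; the case for acting rests on the very low cost.

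**What to change.** In Statistical methods for primary and secondary outcomes (20a), replace the own-baseline adjustment with one sentence: both co-primary models are adjusted for T1 PHQ-9 and T1 GAD-7, each with its by-time interaction. Carry the same pair of T1 scores into the SWAT models and the mediation models, which inherit these adjustments.

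The cost is one main effect and three interactions, so four more coefficients per multilevel model with four follow-up times. No new data are needed, and no cases should be lost, since T1 precedes allocation. The change should be fixed before outcome data are seen; adding the score after the attrition results are known would be a post hoc choice.

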**1a. Overview**			
1	Standard^a^	Psychoeducation	It’s about you
2	Track choice^b^	Behavioral activation I	Map your activities
2	Track choice^b^	Anxiety and GAD	Anxiety and constant worry
3	Track choice^b^	Behavioral activation II	Change through action
3	Track choice^b^	Anxiety and exposure	Anxiety
4	Tailored choice^c^	Rank #1	
5	Tailored choice^c^	Rank #2	
6	Tailored choice^c^	Rank #3	
7	Standard^a^	Acceptance	Acceptance
8	Standard^a^	Maintenance	Continue to take care of yourself
**1b. Tailored choice. All elective module options are presented to participants at the start of their treatment program. The participant then ranks the top three preferences.**			
N/A	Tailored choice^c^	Emotion and affect regulation	Everything we feel
N/A	Tailored choice^c^	Cognitive restructuring	Change your thoughts
N/A	Tailored choice^c^	Stress management	Manage stress
N/A	Tailored choice^c^	Relaxation	Relaxation
N/A	Tailored choice^c^	Sleep hygiene	Change your sleep
N/A	Tailored choice^c^	Social anxiety	Anxiety and social contact
N/A	Tailored choice^c^	Panic anxiety	Anxiety and panic
N/A	Tailored choice^c^	Perfectionism	Being perfect?

Note: Each participant’s individual treatment plan is manually coded onto the platform following randomization. For all participants, access to standard and tailored materials is given automatically, in sequence

^a^Standard: The module is provided to all participants

^b^Track choice: The module is assigned on the basis of the participant’s main problem area

^c^Tailored choice: The participant selects three modules. Access is provided manually by the guide assigned to the participant, both for the guided and unguided groups

In both the guided and unguided arms of the intervention, a guide with basic CBT skills will provide an initial telephone conversation to offer each participant an opportunity to prepare for the treatment and, optionally, to consider which of the depression or anxiety tracks to select and which three elective modules to choose. For participants in the unguided arm, the self-help nature of the intervention will be explained, and information will be given that technical questions will be answered by the treatment site support team, and that any questions about the research project should be directed to the principal investigator. Participants in the waitlist arm will be offered the self-help version of the intervention 6 months after recruitment. No initial telephone conversation will be offered waitlist participants.

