Guides, hereafter also referred to as therapists, are clinical psychology students at the master’s level, or healthcare professionals with basic knowledge of CBT. Therapist guides will all be concurrent participants in a remotely delivered 11-week university-level course on psychological treatment delivered via the internet; they will deliver the treatment as part of the clinical practicum within the course. Prior to initiating treatments, therapists will complete a study-specific practical training workshop on conducting online-CBT treatment, including a study-specific treatment manual. During the treatment practicum, therapists will receive 10 weekly 90-min group supervision sessions by a licensed psychologist with experience in offering internet treatment. Throughout the treatment period, therapists will refer continually to the treatment manual and guidelines, including checklists for weekly tasks. Thereafter, therapists will provide regular written feedback on participant progress within 48 h, with an instruction to spend about 15–20 min per week per participant.

The adaptive treatment strategy offered within the SWAT will entail randomization of each participant qualifying for participation (see SPIRIT items 11b and 11c). Participants in both the guided and unguided arms will be eligible for the ATS. Participants in the guided arm will be offered additional personalized support, the nature of which is clarified in an additional telephone session with the therapist or, if the participant prefers, via written communication. The ATS for participants in the unguided arm will entail standard written guidance, as provided to participants in the guided arm of the RCT. Participants in the waitlist group will not be eligible for participation in the SWAT.

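### The primary models have no guide-level term although the guided arm is treated by assigned guides, so guided vs waiting list is tested with too small a standard error if outcomes correlate within guide

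*Protocol article*

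**What the plan says.** Section 20a of the protocol sets the hierarchy of the co-primary models: "Adaptive intercepts will be added to the models at the participant and university level". The same section says how results will be judged: "We will use the posterior probability of effect and *P*-values for our scientific inference". Secondary outcomes are to be modelled similarly, and the SWAT analyses (section 20b) reuse the primary models with a changed contrast. No guide effect appears in any of them.

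Under Outcomes (12), "The primary contrasts are guided vs. waiting list and unguided vs. waiting list". The sample size section (14) is built on the first of these at 6 months.

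Guide contact is described under Intervention description (11a), including the notes to Table 1:

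- **Both active arms:** "a guide with basic CBT skills will provide an initial telephone conversation". Elective modules are opened by hand: "Access is provided manually by the guide assigned to the participant, both for the guided and unguided groups".
- **Guided arm:** guides also give regular written feedback, "with an instruction to spend about 15–20 min per week per participant".
- **Unguided arm:** "For participants in the unguided arm, the self-help nature of the intervention will be explained". Technical questions go to site support and research questions to the principal investigator. Only those randomized to the adaptive treatment strategy (ATS) later receive written guidance.
- **Waitlist:** no initial call, and the self-help version after 6 months.

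Guides are master's-level psychology students or healthcare professionals, all enrolled in a remotely delivered course, and "they will deliver the treatment as part of the clinical practicum within the course".

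**The concern.** When one person treats several participants, their outcomes may be more alike than those of participants treated by different people. In guided vs waiting list this can happen on one side only: guided participants are nested in guides and waitlist participants are not.

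The two planned intercepts do not deal with this. The participant intercept absorbs repeated measures on one person. The university intercept absorbs where the participant studies, and nothing in the protocol ties a guide to a participant's university.

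With a positive guide ICC, the model variance for this contrast is too small. The P-value and the posterior probability, which are the two stated bases for inference, then both look more certain than they should. The sample size carries no allowance for clustering that would offset this.

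**Working it through.** **The plan's own figure.** Inputs from section 14: d = 0.3, two-sided alpha 0.05, power 0.80, 40% attrition at 6 months. An exact two-sample t-test needs 175.4 per group, rounded up to 176. Then 3 × 176 = 528, and 528 / 0.6 = 880. The stated 176 / 528 / 880 reproduces, with independent observations and no design effect.

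**Model for guided vs waiting list.** Let m be the number of *analysed* participants per guide and n = 176 the analysed number per arm.

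- Design effect, guided arm only: DE = 1 + (m − 1) × ICC; it is 1 in the waitlist.
- Ratio of true to reported SE: r = √((1 + DE) / 2).
- Actual two-sided type I error: 2 × (1 − Φ(1.96 / r)).
- Power at d = 0.3: Φ(0.3 / SE − 1.96), with SE = √((1 + DE) / n).

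**Assumed inputs.** The documents give neither caseload nor ICC. I take 4–10 participants assigned per guide and an ICC of 0.02–0.08. Because 176 per arm is a post-attrition number, the matching m after 40% loss is 0.6 × 4 = 2.4 to 0.6 × 10 = 6. The last three rows show what happens if 4–10 per guide remain in the analysis.

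| Analysed per guide | ICC | DE | r | Type I error | Power at 176 per arm |
|---|---|---|---|---|---|
| any | 0 | 1.00 | 1.000 | 5.0% | 0.80 |
| 2.4 | 0.02 | 1.028 | 1.007 | 5.2% | 0.80 |
| 4.8 | 0.05 | 1.19 | 1.046 | 6.1% | 0.77 |
| 6 | 0.08 | 1.40 | 1.095 | 7.4% | 0.73 |
| 4 | 0.02 | 1.06 | 1.015 | 5.3% | 0.79 |
| 8 | 0.05 | 1.35 | 1.084 | 7.1% | 0.74 |
| 10 | 0.08 | 1.72 | 1.166 | 9.3% | 0.67 |

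Example, third row: DE = 1 + 3.8 × 0.05 = 1.19; r = √(2.19 / 2) = 1.046; 1.96 / 1.046 = 1.87, which gives 6.1%.

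**At the hoped-for 1200.** 1200 / 3 × 0.6 = 240 analysed per arm. In the last row SE = √(2.72 / 240) = 0.106, and power is 0.80. The larger sample restores power. It does not correct the type I error, which depends on r and not on n.

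**Other contrasts.** I attach no figure to unguided vs waiting list, because the documented guide contact there is slight for most participants. In the guided stratum of the SWAT, a guide can have participants on both sides of the comparison, so a shared guide effect largely cancels. In the unguided stratum only ATS participants receive guidance, so the one-sided nesting returns there.

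**The case against.** A reader might infer that the standard errors of both primary contrasts are wrong, because both active arms have assigned guides. The documents do not support that. The unguided arm gets one preparatory call and module release, which is access rather than treatment, and only its ATS subset is later guided. Nor are all guides students; some may be healthcare professionals.

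It is also tempting to say that the SWAT as a whole overstates its precision. Randomization there is by individual within arm, so guide effects largely cancel among guided participants. For guided vs unguided, the protocol does not say whether the same guides serve both arms, and section 20a calls that contrast exploratory.

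The size is open to challenge as well. The ICC and caseload are assumed, and several features should limit variation between guides: fixed platform content, a study manual, weekly checklists, weekly group supervision and short written contact. The type I figures further suppose that guide effects differ but average to zero. If treatment did nothing for anyone, and guides were allocated independently of prognosis, no inflation would arise. Whether guides are treated as random or fixed is partly a choice of inference target.

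These points narrow the claim and make it conditional. They do not remove it for guided vs waiting list: the hierarchy is fixed in the text, the nesting is part of the design, and no other term covers it.

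**Conclusion.** The point holds for guided vs waiting list, conditionally. If outcomes correlate within guide, the reported standard error and P-value are too small. With 4–10 assigned per guide, 40% attrition and an ICC of 0.02–0.08, the true standard error is about 0.7–9.5% larger and type I error is about 5.2–7.4%. With 4–10 analysed per guide these become 1.5–17% and 5.3–9.3%. At an ICC near zero there is no distortion. All of these figures rest on assumed caseloads and ICCs.

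The effect on unguided vs waiting list is probably much smaller. In the SWAT the concern is mainly the unguided stratum. This is a modest weakness in precision on a primary contrast that is cheap to correct, not a flaw that invalidates the analysis.

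**What to change.** 1. In the primary and secondary models, add a partially nested guide-level adaptive intercept for guided participants, set to zero for waitlist participants, in both the Bayesian and the maximum likelihood fits.
2. For unguided participants, allow a separate, smaller guide variance, or examine it in a sensitivity analysis. A single variance shared by both active arms would equate weekly feedback with one call.
3. In the SWAT model, include guide for unguided participants randomized to the ATS.
4. Record the assigned guide in the analysis dataset and report the guide-level SD or ICC.

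The cost is one or two variance terms and a guide identifier. Guides are assigned to participants, so the identifier should be obtainable, but the protocol does not say that it is stored. Intervals will be slightly wider, and the guide variance may be weakly estimated if caseloads are small. No new outcome data or design change is needed.
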